**E. Sample Size considerations**

Design

This is a prospective observational study to evaluate Copeptin as a diagnostic and prognostic marker in neurological and neurosurgical patients.

Analysis

Analysis tools

All relevant clinical and laboratory parameters obtained by interview, clinical tests and reviewing of the medical records will be entered into an Excel® database. Statistical Analysis System (SAS® Institute, Cary, NC, USA) and R for Windows (R Foundation for Statistical Computing, www.r-project.org) will be used for data analysis. Statistical evaluation will include stepwise logistic regression analysis to assess which variables are independently associated with outcome.

Sample size considerations

Our sample size consideration is based on our intention to determine an optimal clinical model to predict the outcome of neurological and neurosurgical patients (based on Barthel index, Rankin scale NIHSS scale and Glasgow outcome scale) (i.e. the prognostic question of the study). To determine an optimal clinical model we will undertake a multivariable regression analysis. It has been demonstrated that multiple regression models with a minimum of 10 to 15 observations per predictor variable reveal good estimates [45]. We will evaluate 18 known predictors (i.e. *age; sex; clinical features* (NIHSS or GCS), *important comorbidities* (coronary artery disease, heart failure, atrial fibrillation, hypertension on admission, previous TIA/Stroke, renal disease, dementia, diabetes); *location of the lesion* (LACS etc.); *stroke subtype by the TOAST criteria*; *therapies* (thrombolysis); *laboratory parameters (*baseline glucose level on admission [46-50], CRP); *body temperature*; *smoking histo*ry) in our multivariate analysis. Therefore, we aim to include a minimum sample size of 180 patients (for 10 observations per predictor) to 270 (for 15 observations per predictor) and a maximum sample size of 360 patients (for 20 observations per predictor). All variables will first be tested one by one against the dependent variable unfavorable outcome (defined either as Barthel index <85 or modified Ranking scale 3 to 6) for the presence of a significant association. Only variables significantly associated with the outcome will be assessed in a multivariate model performed separately for each parameter.

Based on the last year’s data in our hospital, the following number of patients with stroke and neurosurgery will be eligible:

*Patients*

|  | Cases 2003 | Cases 2004 |
| --- | --- | --- |
| Estimated eligible neurosurgical patients | Around 180 | Around 180 |
| Ischemic stroke | Around 300 | Around 300 |

An estimated total of around 480 patients will thus be eligible. With an estimated informed consent of 80% and an estimated loss of follow-up of 10%, approximately 350 patients could be included.

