Plasma sodium concentrations are kept within a narrow range to maintain a constant plasma osmolality. This is predominantly regulated by arginin vasopressin (ADH). ADH is produced in the hypothalamus and stored in and released from the neurohypophysis. Plasma ADH levels begin to fall immediately upon swallowing water, before plasma dilution occurs, allowing prompt excretion of diluted urine [24]. Unfortunately, the measurement of circulating ADH levels is challenging, since the mature hormone is very unstable, largely attached to platelets and rapidly cleared from plasma with a half-life of 5 to 15 minutes. ADH is derived from a larger precursor peptide (pre-provasopressin) along with two other peptides, neurophysin II and copeptin. Released in an equimolar ratio, the amount of copeptin mirrors the production of ADH. Plasma copeptin concentration have recently been shown to be an easy to determine, steady parameter [25,26].

ADH plays not only a critical role in osmo-regulation, but also in the regulation of the hypothalamo-pituitary-adrenal (HPA) axis and, thus, reflecting the individual stress response. “Stressors” such as stroke or hemorrhage are strong stimulators of the release of ADH [27]. Accordingly, elevated ADH levels have been reported in experimental ischemia [28,29]. In a small clinical study, patients with stroke had increased ADH levels as compared to controls, correlating with stroke severity [30]. Early prognostic factors to predict in-hospital mortality and medium/long-term outcome in stroke patients are important to guide and tailor early decision on treatment, discharge from the stroke unit and interventions to prevent deterioration of mobility status. Existing prognostic models for stroke often include impractical predictor variables, lack sufficient predictive accuracy and are, thus, not routinely used. In this context, copeptin may be a new prognostic marker and a helpful tool in the early risk stratification of stroke patients.

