**2.2 DETAILED RESEARCH PLAN**

**A. Objectives**

The objectives of this trial are to evaluate

1. The diagnostic value of copeptin levels in the diagnosis of water imbalance in patients with stroke and patients undergoing intracranial surgery.
2. The prognostic accuracy of copeptin levels and other biomarkers to predict the clinical outcome in patients with stroke and patients undergoing intracranial surgery.

Specific objectives of the study are:

- - 1. **Diagnostic Study:**

**Hyponatremia** will be defined as serum sodium concentration below 135 mmol/L [31].

Specifically, we aim to investigate whether Copeptin levels can facilitate the differential diagnosis of hyponatraemia. Thereby, we will use a standardized clinical algorithm based on medical history, drug history, clinical assessment of the extracellular fluid volume, and laboratory parameters such as plasma and urine sodium concentration, plasma and urine osmolality, creatinine, uric acid, urea, total protein, albumin, TSH, fT4, T3, blood glucose, urea nitrogen, plasma potassium to evaluate the aetiology of hyponatraemia (**figure 1**). In our cohort, wee expect a prevalence of around 20 % (i.e. around 75 patients of the 350 patients derived from the power calculation, see below) to have hyponatraemia. The etiologies are listed in Figure 1 including the estimated relative contributions and the most frequent diagnosis within the subgroup is underlined.

**Figure 1** Diagnostic algorithm of hypotonic hyponatraemia:

We **hypothesize** that overall, included patients will have moderately but significantly higher copeptin levels (around 5pmol/L) as compared to healthy controls (4pmol/L). In patients with hyponatraemia, copeptin levels will be lower as compared to patients without hyponatraemia, however, with a wide range (1.7pmol/L (detection limit) to 15pmol/L). Analysing the subgroup of patients with hyponatraemia, we assume that in patients with SIADH, copeptin levels will be markedly increased (i.e. 12pmol/L), moderately increased (8pmol/L) in hypovolemic hyponatraemia and suppressed in hypervolemic hyponatraemia (<2pmol/L). Importantly, we anticipate to identify SIADH as a co-factor also in some patients with “typical” hypervolaemic and hypovolemic hyponatremia, where ADH disturbances have been neglected previously due to the incapability to assess circulating ADH levels.

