**Overall, the hypotheses are the following**:

1. Copeptin will be a new accurate diagnostic tool to facilitate the differential diagnosis of the etiology of sodium imbalance. Copeptin will have a higher diagnostic accuracy as compared to the routinely used clinical assessment of the extracellular fluid volume by physical examination and laboratory parameters. If copeptin is found to be an accurate tool, we aim to validate our findings in a future intervention study, with the aim to improve the management of neurosurgical and neurological patients with sodium imbalance based on copeptin levels.

2. Copeptin will be a reliable prognostic factor and high-quality predictor for the clinical outcome (i.e. mortality, length of stay in ICU, discharge from ICU, length of hospitalization, clinical outcome within the first week and after three months) of neurological and neurosurgical patients.

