**Statistical Analyses**

Basic statistical analyses will be performed as described in the diagnostic study. We will evaluate 18 known predictors (i.e. *age; sex; clinical features* (NIHSS or GCS), *important comorbidities* (coronary artery disease, heart failure, atrial fibrillation, hypertension on admission, previous TIA/Stroke, renal disease, dementia, diabetes); *location of the lesion* (LACS etc.); *stroke subtype by the TOAST criteria*; *therapies* (thrombolysis); *laboratory parameters (*baseline glucose level on admission [46-50], CRP); *body temperature*; *smoking histo*ry), and copeptin levels in our multivariate analysis. All variables will first be tested one by one against the dependent variable unfavorable outcome (defined either as Barthel index <85 or modified Ranking scale 3 to 6) for the presence of a significant association. Only variables significantly associated with the outcome will be assessed in a multivariate model performed separately for each parameter.

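### Hypothesis 2 is about how well copeptin predicts outcome, but the only prognostic analysis explicitly specified tests association and never compares the clinical model with and without copeptin

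*Protocol*

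**What the plan says.** **What is claimed.** Objective 2 (Protocol, section 2.2 A) is to evaluate "The prognostic accuracy of copeptin levels and other biomarkers to predict the clinical outcome in patients with stroke and patients undergoing intracranial surgery". Hypothesis 2, in the list of overall hypotheses, reads "Copeptin will be a reliable prognostic factor and high-quality predictor for the clinical outcome". The Introduction (2.1) gives the reason: existing stroke models "lack sufficient predictive accuracy and are, thus, not routinely used".

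**What is specified.** The Statistical Analyses of the prognostic study (2.2.2) list 18 known predictors "and copeptin levels in our multivariate analysis". Each is first tested against unfavourable outcome "for the presence of a significant association", and then "Only variables significantly associated with the outcome will be assessed in a multivariate model performed separately for each parameter". Section E repeats the screening step and, under analysis tools, states "Statistical evaluation will include stepwise logistic regression analysis to assess which variables are independently associated with outcome". The level is two-sided 0.05, set in the statistical analyses of the diagnostic study.

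**What else might apply.** ROC curves and AUCs appear once, in the statistical analyses of the diagnostic study. The prognostic section says that its basic analyses follow that section, without saying whether ROC/AUC is among them.

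**The concern.** A test of association and a measure of predictive accuracy answer different questions. The null hypothesis of the screening test and of the copeptin term in the logistic model is an odds ratio of 1. Rejecting it says that copeptin carries some information about outcome. It does not say how much, or whether a patient's predicted risk changes usefully once age, NIHSS or GCS and the other predictors are known. This holds for a fully prespecified model as well as for a stepwise one.

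The Significance part of the Synopsis sees copeptin as a possible guide to early treatment decisions and stroke-unit discharge, and section 2.4 makes later intervention studies depend on the results. If a significant adjusted odds ratio were the main evidence carried forward, those steps could rest on a marker that barely changes prediction.

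**Working it through.** **1. The plan's own figures.** The listed predictors count to 18 without copeptin: age, sex, NIHSS/GCS, eight comorbidities, lesion location, TOAST subtype, thrombolysis, glucose, CRP, temperature and smoking (3 + 8 + 7). Then 18 x 10 = 180, 18 x 15 = 270 and 18 x 20 = 360, as stated in section E. Expected inclusion is 480 x 0.8 x 0.9 = 345.6, against a stated figure of approximately 350. By cohort this is 300 x 0.8 x 0.9 = 216 stroke patients and 180 x 0.8 x 0.9 = 129.6, about 130, neurosurgical patients. No power or effect size is stated, so there is none to reproduce.

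**2. Model for the check.** logit P(unfavourable) = a + bZ + ln(OR)·X, where Z is a standard-normal clinical score and X is standardised copeptin. Assumptions that are not in the protocol:
- event rate 30% or 40%;
- b = 1.3 or 1.8, giving a clinical AUC of about 0.77-0.86 over the scenarios run;
- correlation of X with Z of 0 or 0.4;
- adjusted odds ratio per SD from 1.2 to 2.0.

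The AUC with and without X comes from 1,000,000 simulated patients. Power of the two-sided 5% Wald test is approximately Φ(ln(OR)/SE − 1.96), with SE from the expected information matrix. The univariable filter and stepwise selection are not modelled.

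**3. One scenario in full.** Event rate 40%, b = 1.3, correlation 0.4, OR 1.5, N = 350. ln 1.5 = 0.405 and SE = 0.145, so 0.405/0.145 = 2.80 and power = Φ(2.80 − 1.96) = Φ(0.84) = 0.80. The AUC goes from 0.804 to 0.814. At N = 180, SE = 0.145 x √(350/180) = 0.202, so 0.405/0.202 = 2.00 and power = Φ(0.04) = 0.52.

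**4. Ranges over the eight scenarios, N = 350.**

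| Adjusted OR per SD | AUC gain | Power |
|---|---|---|
| 1.2 | 0.0015-0.003 | 21-30% |
| 1.3 | 0.003-0.006 | 37-54% |
| 1.4 | 0.005-0.010 | 54-74% |
| 1.5 | 0.007-0.014 | 69-87% |
| 1.75 | 0.012-0.026 | 91-99% |

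The rows overlap: in two scenarios with OR 1.4 the gain is about 0.005 and power is 54% and 59%.

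For OR 1.5, power is 42-60% at N = 180 and 49-68% at N = 216 (stroke patients only).

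**5. Reading.** A significant copeptin term can coexist with an AUC gain of about 0.01. With gains of a few thousandths it is significant in roughly one-fifth to somewhat over half of studies at 350 patients, and less often at 180.

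**The case against.** **Association is not shown to be the sole analysis.** A reader might infer from section E that nothing but association will be examined. The text does not support that. The regression is something the evaluation will include, the stated aim is an optimal model to predict outcome, and the prognostic section borrows basic analyses from a section that plans ROC curves and AUCs. The ROC sentence there is not itself limited to hyponatraemia. This stands, so a descriptive AUC for copeptin may be intended.

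**The test is not generally likely to reject for a negligible gain.** A reader might also infer that a nearly useless marker would probably come out significant. For odds ratios of 1.2-1.3 the working shows power of 21-54% at 350 patients. Every effect size, event rate and baseline AUC behind these figures is assumed. This stands too: the test can reject, and how often is unknown.

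**Hypothesis 2 names no comparator.** Hypothesis 1 claims superiority over routine assessment; hypothesis 2 does not. Copeptin's own AUC therefore bears directly on its prognostic accuracy and belongs in the assessment. But the Introduction faults existing models for insufficient accuracy, and copeptin is to be analysed alongside 18 known predictors. What it adds to them is a natural part of the question, and a stand-alone AUC cannot show it.

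**The SAP may settle the details.** The resampling method and similar details can be left there. The point is narrower: the protocol does fix a prognostic analysis, and what it fixes does not measure what hypothesis 2 claims.

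**No passage equates P<0.05 with a high-quality predictor.** That is correct. The study is called exploratory, so the misuse is a risk and not a stated intention.

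**Conclusion.** The point holds as a mismatch between claim and analysis. Objective 2 and hypothesis 2 are about accuracy and quality of prediction. The explicitly specified prognostic analysis is significance screening followed by stepwise logistic regression for independent association. No comparison of the clinical model with and without copeptin is stated, even if a copeptin AUC is carried over.

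The mismatch itself needs no assumption. Its size does: under the assumed inputs, at about 350 patients, an odds ratio of 1.5 per SD is significant with 69-87% power for an AUC gain of 0.007-0.014. The same calculation shows that rejection is far from certain for smaller effects or at 180 patients. Because the study is exploratory and the remedy uses data already planned, this should be corrected, but it does not undermine the study's conduct.

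**What to change.** In the Statistical Analyses of the prognostic study and in section E, state that hypothesis 2 is assessed within each cohort by:
- the AUC of copeptin alone for the defined unfavourable outcome;
- the AUC of the clinical model, with known predictors such as age and NIHSS or GCS kept in, fitted with and without log-transformed copeptin;
- the optimism-corrected difference between those AUCs with a bootstrap 95% confidence interval, and the calibration of both models.

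Judge the difference against a minimum worthwhile gain that the investigators fix in advance. An interval judged only against zero would test essentially the same null as an odds ratio of 1 and would leave the problem in place. Report the copeptin odds ratio as evidence of association only.

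**Cost.** Wording and a bootstrap in the planned SAS or R; no new data. The prognostic claim becomes harder to make. The neurosurgical cohort, at about 130 patients, supports only a reduced model and an imprecise estimate, which the protocol should acknowledge.

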g) Clinical symptoms of hyponatraemia will be evaluated on admission and in case of sodium imbalance in neurological patients. In patients undergoing intracranial surgery we will evaluate clinical symptoms daily. Specifically we will monitor the presence of headache, anorexia, nausea, vomiting, muscle cramps and aches, seizures, confusion, apathetic or lethargic development.
h) Routine/Standard laboratory tests: routine blood sampling including: hematocrit, blood urea nitrogen, bicarbonate, total protein, albumin, uric acid serum and urine electrolytes, urine and serum osmolality, creatinine, lipids, TSH, fT4, T3, and basal cortisol. All blood sampling will be done before any food intake, or smoking, if feasible (both, upright position and smoking will potentially elevate ADH and Copeptin levels). Alternatively, influencing factors will be monitored.
i) Imaging : Computer tomography or MRI of the neurocranium (T1, T2, diffusion-weighted image sequence, with or without contrast), if indicated magnetic resonance angiography or conventional cerebral angiography. We will record the time-points of contrast agent application.

Stroke patients will also be classified on the basis of the vascular territory of the ischemic lesion as follows: total anterior circulation syndrome (TACS), partial anterior circulation syndrome (PACS), lacunar circulation syndrome (LACS), posterior circulation syndrome (POCS).

j) Further investigations: Stroke patients will have neurosonography, echocardiography, standard 12-leaf electrocardiography and 24 –hour electrocardiography and then will be classified by etiology of strokes according to Trial of Org 10172 in acute Treatment (TOAST) stroke subtype classification, which differs between large artery atherosclerosis, cardioembolism, small-artery occlusion, other etiology, and undetermined etiology [42].

Importantly, all these investigations are currently performed in the routine setting. Therefore, no additional costs will be charged to the patient, the health care provider or the health insurances.

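### The 180/270/360 targets do not give the stated 10/15/20 observations per predictor once copeptin is counted, and they count patients where a logistic model is limited by the smaller outcome class

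*Protocol*

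**What the plan says.** Protocol section E, repeated in the Analysis paragraph of the Synopsis, gives one justification for the size of the study: "It has been demonstrated that multiple regression models with a minimum of 10 to 15 observations per predictor variable reveal good estimates". It continues "We will evaluate 18 known predictors", lists them, and concludes "Therefore, we aim to include a minimum sample size of 180 patients (for 10 observations per predictor) to 270 (for 15 observations per predictor"), with a maximum of 360 at 20 per predictor. The same section names stepwise logistic regression and a binary unfavourable outcome (Barthel index below 85, or Rankin 3 to 6). Variables are first tested singly, and only significant ones go forward.

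The Statistical Analyses paragraph of the Prognostic Study repeats the same 18 and then adds "and copeptin levels in our multivariate analysis".

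Under Baseline data collection, lesion location has four classes (TACS, PACS, LACS, POCS) and TOAST subtype has five: "large artery atherosclerosis, cardioembolism, small-artery occlusion, other etiology, and undetermined etiology".

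Section E ends with a recruitment forecast from about 300 ischemic stroke and 180 neurosurgical patients a year: "With an estimated informed consent of 80% and an estimated loss of follow-up of 10%, approximately 350 patients could be included". Section A describes that figure differently, speaking of a share "of the 350 patients derived from the power calculation, see below".

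**The concern.** The observations-per-predictor ratio is the only argument offered for the sample size, so it should hold for the model that will be fitted. Two things speak against that. The predictor count leaves out copeptin, the marker the study exists to evaluate. And the rule is applied to patients, although a binary outcome in a logistic model carries information according to its rarer category. No expected rate of unfavourable outcome is given, so a reader cannot convert patients into outcomes.

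At stake is how stable the copeptin odds ratio is and how optimistic the final model looks. As written, the protocol would accept 180 patients as enough for reliable estimates.

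**Working it through.** **Reproducing the plan's figures.** The list in section E has age, sex, NIHSS or GCS (3); eight comorbidities (11); location, TOAST, thrombolysis (14); glucose, CRP, temperature, smoking (18). Copeptin is not among them.
- 18 × 10 = 180; 18 × 15 = 270; 18 × 20 = 360. All exact.
- 480 × 0.80 × 0.90 = 345.6, stated as about 350. This agrees.

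**Step 1: count copeptin.** 18 + 1 = 19 terms.
- 180/19 = 9.5; 270/19 = 14.2; 360/19 = 18.9, against the stated 10, 15 and 20.

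**Step 2: count factor levels.** This assumes that location and TOAST enter as categories and every other predictor uses one parameter. Location needs 3 parameters and TOAST 4, so the total is 16 + 3 + 4 + 1 = 24.
- 180/24 = 7.5; 270/24 = 11.3; 360/24 = 15.0.

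**Step 3: count outcomes.** The smaller class is at most N/2, whatever the rate.

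| N | Largest possible smaller class | Per term (19) | Per parameter (24) |
|---|---|---|---|
| 180 | 90 | 4.7 | 3.8 |
| 270 | 135 | 7.1 | 5.6 |
| 345.6 | 172.8 | 9.1 | 7.2 |
| 360 | 180 | 9.5 | 7.5 |

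These are ceilings, reached only with an even split. With an assumed 25% to 50% unfavourable outcome (the protocol gives no rate), the expected 345.6 patients yield 86.4 to 172.8 outcomes: 4.5 to 9.1 per term, or 3.6 to 7.2 per parameter.

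**Step 4: follow-up loss.** The three targets are worded as patients to be included, and the outcome is read at 3 months.
- 180 × 0.9 = 162; 162/18 = 9.0, or 162/19 = 8.5 with copeptin.
- For 180 patients with outcome, 180/0.9 = 200 must be enrolled.

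**Step 5: cohorts, if modelled separately.** The combined factor is 0.80 × 0.90 = 0.72, assumed equal in both groups.
- Neurosurgery: 180 × 0.72 = 129.6. Without location, TOAST and thrombolysis, which are stroke variables, and with copeptin, there are 18 − 3 + 1 = 16 terms: 129.6/16 = 8.1 patients per term.
- Stroke: 300 × 0.72 = 216; 216/19 = 11.4 per term, or 216/24 = 9.0 per parameter. The 300 is labelled ischemic stroke only, while the inclusion criteria also admit hemorrhagic stroke and TIA, so 216 is only a guide.

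**Step 6: the favourable side.** Expected pooled sample, counted in patients: 345.6/19 = 18.2 per term; 345.6/24 = 14.4 per parameter. Both satisfy the 10 to 15 rule as the protocol words it.

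**Step 7: the origin of the 350.** Section E states no effect size, significance level or power for it. The figure is eligible patients × consent × retention, which is a feasibility count.

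**The case against.** The strongest reply is that nothing is miscalculated. The products are exact, the list does count to 18, and recruitment is consecutive with about 350 expected, so the 180 floor may never bind. At that expected size the patient-based rule is met even with 24 parameters. All of this stands. The finding is therefore about what is counted and about the stated minimum.

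A reader might infer that the plan ignores loss to follow-up. It does not: the forecast deducts 10%, so the 350 is already net. Only the three targets are not inflated.

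A reader might also infer that a full 24-parameter model is planned and will be overfitted. The protocol plans no such model. It screens singly and selects stepwise, and it does not say how the two factors are coded, which an analysis plan may settle. This removes the claim about a full model but not the concern, because screening and selection test every candidate on the same data. The ratio that matters is outcomes per candidate, not per retained term.

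Nor is it settled that stroke and neurosurgery are modelled separately. The two prognostic questions are posed apart, with partly different scales, but section E speaks of one optimal model for both groups. The cohort figures are conditional on that.

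The power-calculation label changes no number, and the hypernatremia paragraph points to sample size considerations instead. It remains a wrong description of where the 350 comes from.

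**Conclusion.** The concern holds in limited form and should be fixed. Two results need no outside assumption. With copeptin counted, the minimum of 180 gives 9.5 observations per predictor, below the plan's own 10. Counted by the smaller outcome class, none of the three targets, nor the expected 346, can reach 10 per term with 19 terms, whatever the outcome rate. Applying the figure of 10 to outcomes is a conventional reading of the rule for logistic models; the protocol itself speaks only of observations.

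The other results are conditional: 7.5/11.3/15.0 patients per parameter on categorical coding of TOAST and location; 4.5 to 9.1 outcomes per term at 346 on a 25% to 50% rate; 8.1 patients per term in neurosurgery on a separate model.

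The documents do not support the broader conclusion that the study falls short of its own rule at the size it expects to reach. Counted in patients and pooled, it meets it. For a study that calls itself exploratory and observational, this is a correction to its justification and candidate list, not a reason to enlarge it.

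**What to change.** Keep planned enrolment and rewrite section E and the matching Synopsis text:

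- Restate the ratios with copeptin and factor levels counted.
- State an assumed rate of unfavourable outcome and the resulting outcomes per candidate parameter, pooled and also per cohort if the cohorts are modelled separately.
- Limit the pre-specified candidate parameters to about one per 10 in the smaller outcome class, or use penalised estimation with copeptin forced in. At 25% to 50%, the pooled limit is 86.4/10 to 172.8/10, or about 8 to 17 parameters. For neurosurgery alone it is 32.4/10 to 64.8/10, or about 3 to 6.
- State the minimum as patients with outcome: 180 with outcome means 200 enrolled.
- Leave location, TOAST and thrombolysis out of any neurosurgical model.
- In section A, replace the reference to a power calculation by one to a feasibility estimate.

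No extra patients are needed beyond those expected. The price is a less favourable stated ratio and a candidate list that may have to be cut substantially, or a penalised model in place of simple stepwise selection.
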